### Data Analysis

Descriptive statistics will be presented for the collected variables, overall and according to the randomization group; for categorical variables absolute and relative frequencies; for continuous variables mean, standard deviation, median, 25th-75th percentile, minimum and maximum. Baseline characteristics of the two study arms will be listed. Cox modeling will be used to perform the primary analysis and assess the association between treatment (traditional vs. device-managed) and the primary endpoint. Hazard ratios and their 95% confidence intervals will be presented together with Kaplan-Meier cumulative survival and with event rates (per 100 persons per year) in each group. The model will include the following potential confounders: evidence of AT/AF in the patient's medical history or recorded by the device before randomization and patients' response to CRT at randomization. In particular, group effects will be tested by interaction terms comparing the treatment effect in patients who are or are not responders to CRT at randomization. Competing events (causes of death other than cardiovascular, transplant or ventricular assist device implant) will be censored at the time they occur. The primary analysis will be done according to Intention to treat (ITT) i.e. automatic shocks programmed according to randomization. Survival analysis techniques will be used to evaluate time-to-event for the evolution to chronic AF and for both subgroup analyses (CRT responders and AT/AF). In case the primary endpoint is fulfilled, additional post-hoc analyses will be performed. In particular a positive response to CRT responsiveness will be analyzed with respect to the planned variables by means of a logistic regression model. The device's ability to manage and correctly classify atrial arrhythmia will be evaluated considering the sensitivity, specificity and accuracy of the device's classification compared to that made by the Event Committee. Quality of life scores, number and total duration of hospital admissions (for all causes, cardiac causes and for heart failure), total duration of AF and total costs will be compared between the two study arms after 3 years using the appropriate statistical test, according to distribution. For economic analysis costs are estimated for hospitalization (reasons, entry date, duration, department), interventions and instrumental examinations performed. A P value of at least 0.05 will be used for statistical significance.

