## Methods/Design

### Study Design and Objectives

The TRADE-HF is a prospective, open-label, randomized, multi-center, two parallel arm study. The study has been approved by the local Ethic Committees of all 20 participating centers and has been registered to http://www.clinicaltrials.gov site (NCT00345592). Enrollment started in November 2006. The steering committee of the study is responsible for the study design and its amendments.

Primary objective of the TRADE-HF study is to demonstrate a reduction in the combination of hospitalizations for cardiovascular causes or death for cardiovascular causes or development of permanent AF, using a device-based treatment of atrial arrhythmias (i.e. automatic therapy) compared to a traditional approach including hospitalization for symptoms and and/or in-hospital treatment of AT/AF (i.e. traditional therapy). Automatic therapy implies that atrial arrhythmias are detected by the device itself which treats the rhythm automatically within 3 hours after episode onset with a predetermined sequence of programmed electrical therapies (anti-tachycardia pacing and electrical shock). On the other side in the traditional arm automatic shock therapy is not active; therefore, patients who will experience symptomatic atrial arrhythmias at home will refer to their center, where treatment of the atrial arrhythmia will be done according to center's practice (e.g. drugs, external cardioversion, device shock commanded by the physician in a hospital environment). Hospitalizations for cardiovascular causes will include any unplanned cardiac cause hospitalization including day hospital, access to the emergency units and in-hospital procedures of AT/AF cardioversion. Permanent AF is considered as any form of AF that is found to be refractory to drug or electrical therapy, for which the physician resigns to take additional actions to restore sinus rhythm and that persists additionally for at least one month. After obtaining informed consent, a three-month observation period ensues, during which the device parameters are optimized, data on atrial arrhythmias are collected and patient's response to the device treatment is assessed. Thereafter, patients are randomized to the two different treatment arms, automatic and traditional therapy in a 1:1 ratio. After being randomized, patients are followed for three years to assess endpoints. The study flowchart is shown in figure 1.

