### Interventions and Follow Up

After obtaining informed consent, patients' baseline data are collected, including demographic background and medical history. A clinical evaluation performed at the time of enrollment includes NYHA class assessment, an electrocardiogram, an echocardiogram and Qol assessment using the Minnesota-Living With Heart Failure questionnaire. During the three-month observation period before randomization, we collect data on the incidence of supraventricular arrhythmia and clinical events; deaths from any cause or chronic atrial fibrillation before randomization are considered dropouts. Patients are randomized by means of a centralized, computer-generated randomization list, with a 1:1 ratio; given that both patients and physicians are aware of the randomized treatment and that patients are specifically trained to manage their symptoms in two different ways depending on the study arm, patients and investigators are not blinded with respect to treatment. At the randomization visit, NYHA class, QoL and atrial and ventricular function are assessed (the latter by echocardiography) in order to evaluate the response to CRT. After randomization, patients are followed up for a total duration of 3 years, with planned ambulatory visits every 6 months.

At follow-up visits a clinical assessment is performed including NYHA class staging, ECG and medical therapy. QoL assessment and echocardiography are mandatory one and two years after randomization. Data regarding events such as hospitalization are collected over the entire follow-up period.

Device shocks and all interventions performed to treat atrial arrhythmias (drug, electrical or other therapy, repeated or not) are collected for both study arms. A protocol for the management of atrial arrhythmias in the traditional arm has not been predefined, but left to center's specific therapeutic practice and decision making, and may range from simple observation of the response to drugs of the hospitalized patient to repeated attempts of internal cardioversion done with the device in a in-hospital environment. The only requirements for this arm are 1) automatic shock set to "off" and 2) arrhythmia treatment performed at in-hospital environment.

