### Sample Size

Patients treated for CRT in two large randomized clinical trials, the COMPANION [13] and CARE-HF [14] studies, yielded a respective incidence of 62% and 38% in deaths or hospitalizations due to cardiac reasons after a two-year follow-up period. According to the AFFIRM study [22], the evolution to chronic AF may range between 20% and 25% after two years, in patients who are likely to experience recurrent AT/AF. In HF patients, the prevalence of AF is reported to vary from 10% to 50%, with higher values in older patients and in those with superior NYHA class [23]. Additionally, the incidence of new-onset AF in these patients ranges from 3% and 10% per year [23]. A study of a large cohort of heart failure patients has recently revealed that around one third of hospitalized patients had ECG evidence of AF [24]. Based on these data, we assumed that around 35% of patients in both study arms of the TRADE-HF study will have experienced at least one episode of atrial arrhythmia after three years and that around 60% will have experienced at least one hospitalization for cardiac reasons or persistent/chronic AF or death from cardiovascular causes. Patients treated automatically with the device are expected to have a lower rate of events. The effectiveness of treating AT/AF with a dual-defibrillator is very high and reported to be around 90% in different settings [15,16]. Assuming a 60% risk for combined endpoints in the traditional arm versus a 43% risk in the device-managed arm, using a two-tailed alpha of 0.05, with a Cox proportional hazards regression model the study will need a total of 360 patients (180 per group) in order to achieve a power of 90% and demonstrate a difference in primary endpoint rates among patients in the device-managed arm versus those in the traditional arm. Assuming a 15% attrition rate during the study, due to loss to follow-up or failure to adhere to the study design, the total sample size will amount to 414 patients (207 per group).

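### The primary Cox model uses disease severity only as one yes/no change and age not at all; adding the recorded baseline levels would gain some power at little cost

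*Protocol article*

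**What the plan says.** In the protocol article, Data Analysis makes a Cox model the primary analysis and lists what it adjusts for: "The model will include the following potential confounders: evidence of AT/AF", from the history or from device recordings before randomization, and CRT response at randomization. It also plans a treatment-by-response interaction test. No other covariate is named.

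Study Design and Objectives (text under Figure 1) defines CRT response as a yes/no change. It combines a relative change in LVEF or LVESV with a functional criterion based on NYHA class or Minnesota score.

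Interventions and Follow Up shows what is on file by time zero: "At the randomization visit, NYHA class, QoL and atrial and ventricular function are assessed", the last of these by echocardiography. Enrolment data are described as "including demographic background and medical history", so age is implied rather than named. The Minnesota questionnaire is the QoL instrument named at enrolment.

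**The concern.** In a randomized trial, covariates are worth adjusting for mainly because they predict outcome; confounding, the reason the article gives, is already dealt with by randomization. The composite consists of cardiovascular admission, cardiovascular death and permanent AF, so how ill the patient is when follow-up starts is a natural candidate predictor.

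CRT response is a weak stand-in for that. It records whether the patient changed, not where the patient stands. On the LVEF limb, a rise from 20% to 24% qualifies (24/20 = 1.20), while a rise from 34% to 40% does not (40/34 = 1.18), although the second patient has much the better ventricle at randomization. On the functional side, a NYHA II patient can qualify by staying stable.

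Omitting a prognostic level from a Cox model moves the estimated hazard ratio toward 1 and costs some power. Here the levels need no new data collection, so the lost power buys nothing.

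**Working it through.** **Inputs from the article.** Risks: "Assuming a 60% risk for combined endpoints in the traditional arm versus a 43% risk in the device-managed arm". Test: "using a two-tailed alpha of 0.05". Target power 90%. Allocation: "automatic and traditional therapy in a 1:1 ratio". Evaluable patients: 360.

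**Input assumed.** The prognostic strength of the unused levels, beyond the two planned factors, is not in the documents. It is varied as the SD of a normally distributed score on the log-hazard scale, from 0.2 to 0.9. A patient one SD above average then has a hazard e^0.2 = 1.22 to e^0.9 = 2.46 times the average.

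**Step 1: reproduce the plan's own figure.**
- Hazard ratio = ln(1 − 0.43)/ln(1 − 0.60) = ln(0.57)/ln(0.40) = 0.613.
- Mean risk = (0.60 + 0.43)/2 = 0.515, so 360 patients give 360 × 0.515 ≈ 185 events.
- Freedman: (1.960 + 1.282)² × [(1 + 0.613)/(1 − 0.613)]² ≈ 183.1, taken as 184 events; 184/0.515 = 357 patients.
- Two proportions: [1.960√(2 × 0.515 × 0.485) + 1.282√(0.60 × 0.40 + 0.43 × 0.57)]²/0.17² = 179.5, so 180 per arm, 360 in total.
- Schoenfeld: 177 events, 344 patients; at 360 patients it gives 91.4% power.

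The stated 360 is reproduced and claims no gain from covariates.

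**Step 2: simulate the effect of adding a prognostic score.** There were 4,000 trials per setting, N = 360, exponential survival within each patient, and marginal risks held at 60% and 43%. Each trial was analysed by Cox Wald test without and with the score.

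| SD of log-hazard | Power without | Power with | Gain (points) | SE of log HR, without / with |
|---|---|---|---|---|
| 0 (useless) | 91.3% | 91.0% | −0.3 | 0.1495 / 0.1498 |
| 0.2 | 91.7% | 92.1% | 0.4 | 0.1496 / 0.1499 |
| 0.3 | 91.7% | 93.1% | 1.4 | 0.1495 / 0.1499 |
| 0.4 | 91.4% | 93.9% | 2.5 | 0.1495 / 0.1500 |
| 0.5 | 92.2% | 95.2% | 3.0 | 0.1495 / 0.1501 |
| 0.7 | 92.7% | 97.7% | 5.0 | 0.1494 / 0.1504 |
| 0.9 | 92.6% | 98.8% | 6.2 | 0.1497 / 0.1512 |

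The simulation error of one power figure is √(0.92 × 0.08/4000) = 0.0043, or 0.4 points. Both analyses use the same simulated trials, so the differences are steadier than that, but the gain at SD 0.2 is small against it.

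**Step 3: see where the gain comes from.** The standard error stays level or rises slightly. Power rises because the adjusted hazard ratio lies further from 1; at SD 0.5 it is 0.585 against 0.610.

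**Step 4: ask whether CRT response already captures the levels.** A second simulation drove outcome by severity at randomization. It assumed an enrolment-to-randomization correlation of 0.7 and defined response as improvement beyond 0.2 SD. For log-hazard SD 0.4/0.6/0.8, power at 60% versus 43% with 360 patients was about 90/92/92% unadjusted, 90/92/92% with the responder flag, and 93/96/98% with the level. Under these assumptions the flag recovers about 0 to 1 point.

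**Step 5: check that the model can carry the terms.** Arm, the two planned covariates, NYHA class as one term, LVEF, Minnesota score and age make seven parameters: 185/7 ≈ 26 events per parameter.

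**The case against.** The strongest reply is that nothing here is wrong. A prespecified Cox model with two pre-randomization covariates is a valid analysis of a randomized trial, and the sample size meets its target without further adjustment. That stands: this is an improvement in efficiency, not the correction of an error.

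Other parts of the reply also stand and limit the point:

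- A reader might infer that adjustment would narrow the confidence interval for the hazard ratio. It would not (Step 3). The gain belongs to a conditional hazard ratio, which is a somewhat different quantity from the marginal contrast used for sizing.
- A reader might say that NYHA class, LVEF and Minnesota score are left out. That is too strong, because their changes are built into CRT response. Only age is wholly absent.
- The main simulation compares against a model with no covariates, not the planned model. Its gains apply to the plan only if the score is read as prognostic information beyond the planned factors.
- The article describes AF prevalence among heart failure patients "with higher values in older patients and in those with superior NYHA class". That concerns AF prevalence, not prediction of this composite.
- Larger gains appear if the true effect is smaller than assumed, but the documents contain no such scenario.

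What does not stand is the suggestion that the responder flag makes the levels redundant. A dichotomised change is not a level, and Step 4 shows how little it may recover.

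**Conclusion.** The plan is sound and reaches its stated power, but it forgoes some more by using severity only as one dichotomised change. At the design effect with 360 patients the gain from adding the levels is about 0.4 to 3 points for a weak to moderate score (SD 0.2 to 0.5) and 5 to 6 points for a strong one (SD 0.7 to 0.9). If the levels predict nothing, the loss is about 0.3 points.

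The direction is well supported; the size is not, because it rests on assumed prognostic strength. NYHA class IV is an exclusion criterion and all patients are CRT candidates, so the spread of severity is probably narrow and the gain probably toward the low end.

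One might also conclude that CRT response should come out of the primary model to make room. The documents do not support that: the Discussion reports links between CRT response and AF, and there are ample events for all the terms.

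**What to change.** In Data Analysis, keep AT/AF evidence and CRT response as covariates and add four: NYHA class, LVEF (continuous) and Minnesota score, each from the randomization visit, and age. Fix this list before any outcome data by arm are seen. State that the treatment-by-CRT-response interaction is tested in a separate model, and report the hazard ratio without the four added covariates beside the primary one.

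The cost is a few sentences of analysis wording and no new measurements. There are two small downsides. The primary hazard ratio becomes conditional on more covariates and should be labelled so. Some randomization-visit values may also be missing, so a simple prespecified rule is needed to ensure that no randomized patient is dropped for want of a covariate.

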### Patient Selection

Patients who meet all of the following criteria are considered eligible to take part in the study: 1) chronic (>6 weeks) symptomatic HF despite stable, optimal drug therapy for HF and AF, 2) patients scheduled for and implanted with a cardiac resynchronization device with defibrillator backup according to current guidelines. 3) age 18 or above, or of legal age to give informed consent according to specific national regulations. Principal exclusion criteria include: 1) chronic or persistent atrial fibrillation refractory to medical or electrical therapy 2) valve disease, and/or patients with or who are likely to receive a mechanical tricuspid valve during the course of the study 3) patients who have undergone (or are scheduled to undergo) an intervention of atrial fibrillation ablation 4) cerebral vascular event or transient ischemic attack within 12 months of implantation which lead to significant impairment 5) life expectancy of less than 1 year due to other medical conditions 6) NYHA class IV. According to the listed criteria, patients are not selected on the basis of atrial arrhythmia recurrence, except for chronic/persistent AF.

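### The planned Kaplan-Meier curves overstate the composite's actual three-year risk, and a transplant or VAD as first event is not counted; the Cox hazard ratio is unaffected

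*Protocol article*

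**What the plan says.** All places are in the protocol article.

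- **Endpoint** (Study Design and Objectives): the primary objective is a reduction in "the combination of hospitalizations for cardiovascular causes or death for cardiovascular causes or development of permanent AF". Transplant and VAD implant are not components. On the hospital component the section adds: "Hospitalizations for cardiovascular causes will include any unplanned cardiac cause hospitalization". It also counts day hospital, emergency-unit access and in-hospital cardioversion.
- **Primary model** (Data Analysis): "Cox modeling will be used to perform the primary analysis".
- **Competing events** (Data Analysis): "Competing events (causes of death other than cardiovascular, transplant or ventricular assist device implant) will be censored at the time they occur".
- **Display** (Data Analysis): "Hazard ratios and their 95% confidence intervals will be presented together with Kaplan-Meier cumulative survival", together with person-time event rates in each group.
- **Permanent AF on its own** (Data Analysis): "Survival analysis techniques will be used to evaluate time-to-event for the evolution to chronic AF". No estimator or censoring list is given for this analysis.
- **Planning risks** (Sample Size): "Assuming a 60% risk for combined endpoints in the traditional arm versus a 43% risk in the device-managed arm", over three years of follow-up.

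**The concern.** The plan names three events as competing and then pairs them with an estimator that treats them as ordinary censoring. Two separate consequences follow.

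**Displayed risk.** With competing events censored, one minus Kaplan-Meier describes a setting in which non-cardiovascular death, transplant and VAD do not occur. It is therefore higher than the proportion of randomized patients who reach the composite as defined. Three-year risk is also the scale on which the trial was planned, so readers will compare the curves with 60% and 43%.

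**Uncounted events.** The eligibility criteria require "chronic (>6 weeks) symptomatic HF despite stable, optimal drug therapy for HF and AF". In such patients a transplant or VAD implant marks worsening of the disease under study. If it comes by planned admission and before any component of the composite, the patient leaves the risk set without an event.

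The two consequences have different reference points. The curve is too high for the composite as defined, but it lies below the risk of a composite that includes transplant and VAD.

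**Working it through.** **1. The plan's own figure.** Two proportions, 0.60 and 0.43, mean 0.515, two-sided alpha 0.05, power 90%, no continuity correction:

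n per group = [1.960 × √(2 × 0.515 × 0.485) + 1.282 × √(0.60 × 0.40 + 0.43 × 0.57)]² / 0.17² = 179.5, rounded up to 180.

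The stated 360 reproduces and does not depend on this point.

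**2. Displayed against actual risk.** Inputs: 60% and 43% at three years, from Sample Size. The competing-event risk is an assumption, because the documents give none. It is taken as the three-year net risk of the three listed events together, with constant hazards and equal rates in both arms.

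- Event hazard: λ = −ln(1 − risk)/3, which is 0.3054 (traditional) and 0.1874 (device-managed) per year.
- Competing hazard: μ = −ln(1 − c)/3, which is 0.0171 for c = 5%.
- Displayed: 1 − KM = 1 − exp(−3λ).
- Actual: λ/(λ + μ) × [1 − exp(−3(λ + μ))].

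Traditional arm at c = 5%: 0.3054/0.3225 × (1 − 0.40 × 0.95) = 0.947 × 0.62 = 0.587.

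| Assumed competing risk | Traditional: displayed → actual | Device-managed: displayed → actual | Actual difference (displayed 17.0) |
|---|---|---|---|
| 5% | 60.0 → 58.7 | 43.0 → 42.0 | 16.7 |
| 10% | 60.0 → 57.4 | 43.0 → 41.0 | 16.4 |
| 15% | 60.0 → 56.1 | 43.0 → 40.0 | 16.1 |

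The overstatement is 1.3, 2.6 and 3.9 points in the traditional arm and 1.0, 2.0 and 3.0 in the device-managed arm. The difference between arms changes by 0.3, 0.6 and 0.9 points.

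Unequal rates, as an illustration only: with 10% traditional and 5% device-managed the actual difference is 57.4 − 42.0 = 15.4 points. With the rates reversed it is 58.7 − 41.0 = 17.7.

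**3. Does prognosis-linked censoring remove the overstatement?** A simulation let the event and the competing event share a gamma frailty (variance 0.5 or 1), with an assumed competing risk of 3% to 10%. One minus Kaplan-Meier still exceeded the actual cumulative incidence, by 0.4 to 2.1 points.

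**4. Counting transplant and VAD as events.** The assumed three-year risk of transplant or VAD is t, equal in both arms. Composite risk = 1 − (1 − risk)(1 − t). The hazard ratio is (λ₂ + μ)/(λ₁ + μ), with μ now the transplant/VAD hazard. Power is Schoenfeld's at N = 360.

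| t | Composite risk, traditional / device-managed | Hazard ratio | Power |
|---|---|---|---|
| 0% | 60.0 / 43.0 | 0.613 | 91.4% |
| 1% | 60.4 / 43.6 | 0.618 | 90.9% |
| 3% | 61.2 / 44.7 | 0.626 | 89.9% |
| 5% | 62.0 / 45.9 | 0.634 | 88.8% |

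**The case against.** The strongest reply is that the primary analysis is correct as it stands. Censoring competing events in a Cox model is the standard way to estimate a cause-specific hazard ratio, and that estimate needs no assumption that the events are independent. Person-time rates are shown beside the curves, and the sample size is untouched. All of this stands.

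Three stronger readings are tempting, and the documents do not support them.

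- **That the worst heart-failure outcomes are dropped from the endpoint.** Any unplanned cardiac admission or emergency visit already counts, and so does cardiovascular death. A patient admitted in this way before transplant or VAD has met the composite. Only a transplant or VAD that precedes every component is lost. Patient Selection also excludes NYHA class IV, which should limit such cases early on.
- **That the treatment comparison is materially distorted.** At equal competing rates it hardly moves. A larger shift needs rates that differ by arm, and nothing in the documents indicates that they do.
- **That the permanent-AF and cardiovascular-death analyses are biased by the same rule.** The competing-event sentence belongs to the description of the primary model, where cardiovascular death is an event, so listing only other deaths is right there. For permanent AF the article names only survival techniques in general. For cardiovascular death alone it gives no time-to-event method. Either may be settled in an analysis plan that is not shown.

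The reply does not rescue the curves. The article fixes both the censoring and the Kaplan-Meier display, and together they do not give the actual risk of the composite.

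**Conclusion.** The point holds as a matter of display and robustness. The primary hazard ratio, its test and the 360 patients stand. The Kaplan-Meier curves will overstate the three-year cumulative incidence of the composite by about 1.3 to 3.9 points at a displayed 60%, if 5% to 15% of patients would have a competing event. That range and the constant hazards are assumptions; the direction depends on neither. At equal rates of 5% to 10% the difference between arms changes by about 0.3 to 0.6 points. A first-event transplant or VAD goes uncounted, and how often this will happen cannot be judged from the documents.

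**What to change.** 1. Keep the cause-specific Cox hazard ratio as the primary analysis.
2. Replace or accompany the Kaplan-Meier curves with Aalen-Johansen cumulative incidence by arm. Name non-cardiovascular death, transplant and VAD implant all as competing events, so that none is left as plain censoring.
3. Pre-specify one sensitivity analysis of the composite that counts transplant and VAD as events alongside cardiovascular death, with only non-cardiovascular death competing.
4. If the same censoring list is carried over to the permanent-AF analysis, make death from any cause the competing event there, since cardiovascular death also prevents later permanent AF.

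The cost is wording, one extra analysis and slightly lower displayed risks. No new data are needed, because censoring these events when they occur already requires their dates. The sensitivity analysis stays informative: power falls from 91.4% to 88.8% even if transplant or VAD adds an assumed 5% risk in both arms.

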**Figure 1 F1:**
[figure not shown]
**Study flowchart**. RND: Randomization.

Secondary objectives include: the performance assessment of automatic atrial therapies, and a comparison between the automatic-managed and traditional therapy arm of the following outcomes: in-hospital costs, Quality of Life (QoL) scores, number of hospital admissions and the separate components of the primary endpoint.

An exploratory analysis will be done in order to investigate the response to CRT treatment for the enrolled patients. A positive response to CRT is considered a relative LVEF increase ≥ 20% and/or a relative LVESV decrease ≤ 15% measured at echocardiographic recording associated with a functional assessment defined as reduction of at least one NYHA class or of 15 points at Minnesota living with heart failure score for NYHA class III patients or at least stable NYHA class or 10 points decrease at Minnesota living with heart failure score for NYHA class II patients. This definition reflects patient's cardiac remodeling associated to a functional improvement in highly symptomatic patients or at least a stable functional condition in mild symptomatic patients. The proportion of CRT responders will be analyzed at time of randomization and one year after randomization; additionally a correlation, separately at the two time points, will be searched among the proportion of CRT responders, the burden of atrial fibrillation (total percentage of recorded AT/AF episodes: 0; <10%; >10%) and the target site of left ventricular lead (lateral wall vs. other).

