If a primary endpoint event, other than patient death, occurs, the patient continues to be followed over the entire 2-year period in order to assess secondary endpoints. Crossover may occur at any point during the follow-up: patients may withdraw from the device-controlled therapy arm when atrial shock therapy is disabled due to severe discomfort related to shocks or too frequent atrial shock therapies; patients may cross from the traditional therapy to the device-controlled arm when atrial shock therapy is enabled chiefly because the number of hospital admissions for atrial cardioversion becomes too frequent. Patients who present with permanent/chronic AF, regardless of the randomization arm, start rate control therapy with the device's atrial therapy set to off: this is not considered a crossover, as the patient has already reached the primary endpoint.

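### Admissions, hospital days and AF duration are compared as three-year totals with no allowance for time alive and observed, so unequal death or loss between arms would distort them.

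*Protocol article*

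**What the plan says.** All references are to the protocol article.

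- **Secondary objectives** (Methods/Design, after Figure 1): the arms are to be compared on "in-hospital costs, Quality of Life (QoL) scores, number of hospital admissions and the separate components of the primary endpoint".
- **Data Analysis, the quantities:** they are given as "number and total duration of hospital admissions (for all causes, cardiac causes and for heart failure), total duration of AF and total costs".
- **Data Analysis, the method:** "total costs will be compared between the two study arms after 3 years using the appropriate statistical test, according to distribution". No exposure term, and no rule for death or loss, is attached to these outcomes.
- **Data Analysis, the primary endpoint:** hazard ratios are presented "together with Kaplan-Meier cumulative survival and with event rates (per 100 persons per year) in each group", and "Competing events (causes of death other than cardiovascular, transplant or ventricular assist device implant) will be censored at the time they occur". Survival techniques are also named for evolution to chronic AF and for the two subgroup analyses. None of this is extended to the totals.
- **Interventions and Follow Up:** "patients are followed up for a total duration of 3 years, with planned ambulatory visits every 6 months". The same section later says "If a primary endpoint event, other than patient death, occurs, the patient continues to be followed over the entire 2-year period", so follow-up for secondary endpoints ends at death, and the window is given as 2 years in one place and 3 in another.
- **Sample Size:** 15% attrition is assumed, covering loss to follow-up and failure to adhere to the design.

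**The concern.** A count of admissions, a sum of hospital days or a sum of AF time can grow only while the patient is alive and observed. A patient who dies or is lost early carries a low total, which looks the same as few admissions or little AF. For example, if deaths are included, a patient in continuous AF who dies at 6 months accrues about 0.5 × 365 = 183 AF days. A survivor in AF for 20% of 3 years accrues 0.20 × 1,095 = 219. The total ranks the first patient as better off. This pair shows how the measure behaves, not how large an arm-level effect would be.

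Choosing the test by the shape of the distribution does nothing about unequal exposure. Number of admissions is a named secondary objective, and the Discussion presents fewer admissions as a main advantage of automatic therapy. A difference in totals should therefore be readable as a difference in the rate of admission, and as written it may not be.

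**Working it through.** **The plan's own figures.** The protocol gives no figure for these outcomes. Its sample size reproduces. The two-proportion formula with 60% vs 43%, two-sided 5% and 90% power gives [1.96·√(2·0.515·0.485) + 1.2816·√(0.60·0.40 + 0.43·0.57)]² / 0.17² = 179.5, so 180 per arm and 360 in all. With 15% added this is 360 × 1.15 = 414, or 207 per arm. This does not bear on the point beyond fixing the arm size used in step 3.

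**Inputs.** Follow-up of 3 years is from the protocol. Mortality by arm is not given, so the values below are assumptions, shown as a range.

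**1. Effect of exposure alone.** With a constant death hazard and 3-year mortality m, mean observed time is m ÷ [−ln(1 − m)/3].

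| Assumed 3-year mortality | Mean years observed |
|---|---|
| 15% | 0.15 / 0.05417 = 2.769 |
| 20% | 0.20 / 0.07438 = 2.689 |
| 25% | 0.25 / 0.09589 = 2.607 |

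With the same yearly admission rate in both arms, expected totals are proportional to these times:

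- 20% vs 15%: 2.769 / 2.689 = 1.030, so totals are 3.0% higher in the arm with fewer deaths.
- 25% vs 15%: 2.769 / 2.607 = 1.062, so 6.2% higher.
- Equal mortality: ratio 1, no bias.

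The same formula applies to loss to follow-up if m is read as the probability that observation stops.

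**2. Sicker patients both die and are admitted more.** Assume a shared gamma frailty with mean 1 and variance 1, and 20% control mortality. The cumulative death hazard H then satisfies H/(1 + H) = 0.20, so H = 0.25. Mean admissions are proportional to 1/(1 + H), and mean observed time is 3·ln(1 + H)/H.

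| Mortality hazard ratio | H | Ratio of totals | Mean years, this arm vs control | Ratio of rates per patient-year |
|---|---|---|---|---|
| 0.7 | 0.175 | 1.25/1.175 = 1.064 | 2.765 vs 2.678 (1.032) | 1.064/1.032 = 1.03 |
| 0.5 | 0.125 | 1.25/1.125 = 1.111 | 2.827 vs 2.678 (1.056) | 1.111/1.056 = 1.05 |

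The admission rate at a given frailty is the same in both arms, so both ratios should be 1. Totals are off by 6% and 11%. Dividing by follow-up time leaves about 3% and 5%, roughly half, because the arm with fewer deaths keeps frailer patients under observation.

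**3. Effect on a test.** The simulation used 207 per arm, an assumed 0.6 admissions per year with gamma variation between patients, death independent of admission, equal true admission rates, and a Wilcoxon test on the counts at 5%. The rejection rate is about 5% with equal mortality, 6% with a 5-point gap, 8% to 9% with 10 points and 13% to 14% with 15 points.

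**4. The completers-only reading.** If the phrase about 3 years restricts the comparison to patients who reach that point, early deaths drop out and are not given a low total. The groups compared are then selected by survival after randomization. Neither reading accounts for time alive.

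**The case against.** **The method may be open.** A condensed article that calls for an appropriate test leaves room for a full analysis plan to add an offset or a recurrent-event model. This stands in part: the absence of detail is not the point. The article does fix the quantities as totals and the selection rule as distribution, and a plan that follows it would carry the problem over.

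**Stronger readings that the documents do not support.**

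- A reader might infer that mortality is expected to differ by arm because cardiovascular death is in the primary endpoint. Only the composite is assumed to differ (60% vs 43%). The Background says data on improved survival are lacking, and the Discussion cites a large trial in which rhythm control did not reduce cardiovascular death, while allowing that CRT patients may differ.
- A reader might infer that early death is necessarily scored as a good outcome. That holds only if deaths enter the comparison; under the completers-only reading they do not.
- A reader might infer that transplant or an assist device also stops the counts. Those events are censored in the text on the Cox analysis. Hospitalization data are collected over the whole follow-up, and only death is exempted from continued follow-up after a primary event.
- A reader might include total cost in the criticism. A cost that stops at death is a legitimate quantity; the difficulty there is incomplete data from loss.

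**The bias is modest, and deaths will be partly visible.** Both are true. The separate components of the primary endpoint include cardiovascular death, so part of the context will be reported by arm; all-cause death is not named. Total admissions over a fixed horizon, read beside mortality, is also a recognised quantity. These points limit the severity but do not give the totals an exposure term.

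**Conclusion.** The point holds in a limited form. As written, admissions, hospital days and AF duration are compared as totals without regard to time alive and observed, in a trial where follow-up ends at death and attrition is anticipated. Under assumed mortality gaps of 5 to 10 points and equal admission rates, the shift is about 3% to 6% in favour of the arm with more deaths. It could reach 6% to 11% under the assumed shared frailty with mortality hazard ratios of 0.7 and 0.5. It is near zero if death and loss are similar in the arms. All of these sizes rest on assumed mortality, because the protocol states none. The primary analysis is untouched, and the severity is low to moderate.

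**What to change.** In Data Analysis, replace the comparison of totals with the following:

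- **Admissions** (all-cause, cardiac, heart failure): rates per patient-year from a negative binomial model with log follow-up time as offset.
- **AF duration:** percent of device-monitored time spent in AT/AF.
- **Hospital stay:** days alive and out of hospital over the follow-up window, with days after death counted as zero.
- **Each of these** shown with all-cause deaths by arm.
- **Sensitivity analysis:** a joint model for admissions and death, because the offset removes only about half the bias when frailer patients both die and are admitted more.
- **Costs:** keep total cost per patient, reported with survival time by arm and with an adjustment for patients lost to follow-up.

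Reconcile the 2-year period in Interventions and Follow Up with the 3 years given there and in Data Analysis, since this window defines every one of these outcomes.

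The cost is wording and somewhat more analysis. Events, admission dates and durations, and recorded arrhythmia episodes are already collected. The downside is that rates are harder to explain than totals.
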